## Methods and general study design

This study has received approval from the Human Ethics Research Committee at the University of Notre Dame Australia. The study will use a parallel mixed methods design. The research methodology for this study is a phase II, randomised, placebo-controlled crossover trial. The design will include a 2-week eligibility (assessment) period, two 6-week-treatment cycles to allow each participant to take part in both the control and treatment cycles, and two 2-week washout periods (one between both treatment cycles and the other after the second treatment cycle). The 6-week treatment cycles have been selected on the basis of safety, pharmacodynamics, and pharmacokinetics as reported by Ahmed et al. [14], and a 2-week washout period has been shown to be safe and an appropriate length of time for cannabis to metabolise in older individuals [44].

In addition, residential aged-care staff and next of kin perceptions towards the use of CBM oil will be evaluated via surveys administered prior to and upon completion of the study. At the end of the second treatment cycle, the residential aged-care staff and family members will be asked to participate in a follow-up focus group to gather more in-depth information regarding individuals’ perceptions before and after the administration of CBM. Each participant will be in the trial for approximately 4 months (18 weeks), but the duration of the study will last over 12 months in order to recruit participants from a number of aged-care facilities.

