### Adverse events and safety protocol

An adverse events protocol will be put into place to minimise any potential harm or risks of receiving additional medication [14]. This will include participants reporting if they have experienced any adverse events 1 h after the increased dose has been administered (*see* Appendix). If moderate to severe adverse events are recorded (determined as ‘Somewhat worse’ (moderate) or ‘Much worse’ (severe) on the participant’s adverse event record) and these events have not ameliorated by the time for the next dose, the participant will receive the previous best tolerated dose. If the effects of the adverse event(s) have disappeared or become milder and do not interfere with the participant’s daily functioning or well-being, the registered nurse may increase the dose at the indicated rate. Recurrence of adverse events after two attempts to increase the dose will result in the participants remaining at their previous best tolerated dose for the remainder of the intervention period. A participant who experiences an adverse event will stay on the previous dose for another 2 days before the next dose is increased. At the beginning of the titration phase, a staff member at the aged-care facility will be vigilant in monitoring any acute adverse events such as dizziness, discoordination with a danger of falls and injury, and extreme fatigue. Any adverse events recorded will be reported to a facility line manager and will then be communicated to staff during shift changes.

Additional safety monitoring will be completed by a research nurse who will meet with each participant to discuss their adverse event records and measure their heart rate and blood pressure twice per week. In addition, the participant’s weight and non-invasive body composition measures such as lean body mass, bone mass, body fat percentage, and fat mass will be measured once per week using a portable scale. In addition, a nurse-led review will be completed 2 days into the washout periods to monitor the participant’s withdrawal symptoms once no more medication is being administered.

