### Data analysis

#### Quantitative

The results of questionnaires completed on behalf of the aged-care staff, participants and family members will be analysed using IBM SPSS Statistics version 25 software (IBM, Armonk, NY, USA). The responses from the aged-care staff will be the main responses considered for analysis. Where available, participants and family responses will be included for secondary analysis. To examine group differences, the participants will be categorised according to their treatment cycle group allocation (group A or group B). Descriptive statistics will be derived. Each variable will be tested for normality. For those variables that meet the normality assumption, two-sided paired and/or independent *t* tests will be used to examine group differences within and between groups. If the normality assumption is violated, then non-parametric tests such as the Wilcoxon signed-rank test will be used. Within-subject differences of the four measurements between the first and second washout periods will be tested using paired *t* tests to ensure that the washout phase is long enough to rule out any carryover effects [51, 52]. All data collection points will be examined using general linear mixed modelling techniques to see if any changes in behaviour, QOL or pain have occurred over the duration of both treatment cycles. The covariates of weight, average dose of medication, and baseline measures will be controlled for in each model, and any interactions will be tested and reported. The proportion of adverse events during the CBM and placebo phases will be tested and reported for each individual. NPI-NH is the primary outcome measure for this study. All other measures (CMAI, QOL-AD, and Abbey Pain Scale) have been included for secondary analysis. The CMAI will be analysed using the reliability change methodology compared with the NPI-NH to allow small changes to be reported [53]. The α-value will be set at 0.05. In the instance where a participant withdraws halfway through a treatment cycle, the information collected prior to withdrawal will be retained in the study because their personal information will have been de-identified. The data management of the information collected will follow standard university procedures, be stored in a locked cabinet for a period of 15 years, be stored on a password-protected computer, and be backed up regularly in a secure format.

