A number of challenges have been identified in the proposed study. It may be difficult to find those with a dementia diagnosis who have the cognitive capacity to give informed consent, because many experience a loss of short-term memory, intellectual reasoning, rationality, and social skills [1, 2]. This may lead to difficulty in recruiting participants into the trial and excluding those who do not have the capacity to give informed consent; yet, they are potentially the ones who exhibit a greater number of behavioural occurrences. Those who experience mild to moderate dementia still exhibit symptoms such as depression and anxiety and both verbal and physical agitation [2]. However, due to the limited legislation regarding including those who do not have the cognitive capacity to give informed consent in research projects, this limits who can be included in this study. The replication of this study design to include those with a moderate to severe diagnosis would warrant further generalisability of the results. Irreversible progression of cognitive impairment, the associated complications and comorbidities, and frailty of the participants may lead to participants dropping out of the study. To accommodate this, we have included a 20% increase in the sample size. It is also difficult to know if the questionnaires chosen for this study are suitable and sensitive enough to measure the changes attributed to the use of CBM oil, because no ‘gold standard’ exists to measure BPSD. Therefore, both the NPI-NH and the CMAI have been selected to account for the small effects. The pharmacodynamics of the medication will be monitored during the treatment cycles through the use of non-invasive body composition measures and monitoring of heart rate, blood pressure and weight. These measures will be collected by a research nurse external to the aged-care facilities to improve the feasibility of the study, to avoid additional workloads placed on the aged-care staff, and to ensure that each participant is receiving their best tolerated dose. In addition, only one residential staff member has been selected to complete the questionnaires, because they spend a great deal of time with the residents and can report symptoms easily. Independent reviews have not been selected for this study, because they are unfamiliar to the participants, which may lead to inaccuracy in recording of the results.

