**Table Taba:**

	No	Yes (tick box below)				
		Better	Somewhat better	Same as usual	Somewhat worse	Much worse
Drowsiness/fatigue						
Dizziness						
Dry mouth						
Sore throat						
Anxiety						
Nausea						
Memory decline or attention deficits						
Joy or euphoria						
Blurred vision						
Headache						
Paranoia						
Depression						
Lack of coordination						
Diarrhoea						
Appetite						
Sleep disturbance						

To be completed during the titration phase and following the last dose in each treatment arm

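### Withdrawal events in washout are not scheduled for the adverse event form and fall outside the adverse event comparison as worded

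*Protocol article*

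**What the plan says.** The Aims section of the protocol article puts safety in the primary aim, alongside behavioural and neuropsychiatric symptoms.

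- **Withdrawal review.** Under Adverse events and safety protocol, "a nurse-led review will be completed 2 days into the washout periods", and its purpose is "to monitor the participant’s withdrawal symptoms once no more medication is being administered". The Discussion mentions nurse-led reviews in washout again but adds no time point.
- **Washout length.** Methods and general study design justifies it on the ground that "a 2-week washout period has been shown to be safe and an appropriate length of time for cannabis to metabolise in older individuals".
- **Adverse event form.** The note under the Appendix form reads "To be completed during the titration phase and following the last dose in each treatment arm". The Table 1 footnote places recording one hour after dosing on dose-increase days, and on the last treatment day. The form asks about change over the last hour.
- **Analysis.** Under Data analysis, Quantitative: "The proportion of adverse events during the CBM and placebo phases will be tested and reported for each individual".
- **Other contacts.** The four outcome questionnaires are completed on day 56 and day 112, at the end of each washout. The safety section also has a research nurse meeting participants to discuss their adverse event records and measure heart rate and blood pressure twice a week, with weight and body composition weekly. The Abstract gives weekly and fortnightly for these measures. The Discussion says the drug's pharmacodynamics "will be monitored during the treatment cycles through the use of non-invasive body composition measures", together with heart rate, blood pressure and weight.

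**The concern.** The article fixes three things: the day of the withdrawal review, the times of the adverse event form, and the periods that the adverse event analysis compares. They do not fit together. The plan expects that symptoms may follow stopping and looks for them on day 2, but the form has no scheduled use in washout. The analysis is worded for two phases, and washout is neither of them.

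At stake is the safety conclusion. An effect of stopping CBM could be noticed by the nurse and still not enter the comparison on which that conclusion will rest.

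**Working it through.** The plan gives no figure for withdrawal, so the check is on the calendar and on how the sections fit together.

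**1. Washout length.** The first washout runs from day 42 to day 56: 56 − 42 = 14 days, which reproduces the stated 2 weeks. The second runs from the stated day 97 to day 112: 112 − 97 = 15 days. A 42-day second cycle would end on 56 + 42 = day 98, which gives 112 − 98 = 14. The one-day difference does not affect the point.

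**2. Time after the dedicated review.** In the first washout the review falls on 42 + 2 = day 44. That leaves 56 − 44 = 12 days, and 12/14 = 86% of the washout, with no further dedicated withdrawal review. In the second washout the figure is 112 − 100 = 12 days, or 112 − 99 = 13 if the cycle ends on day 97.

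**3. The sections side by side.**

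| Period | Dedicated withdrawal review | Adverse event form scheduled | In the comparison as worded |
|---|---|---|---|
| Cycle 1, to day 42 | none | dose-increase days and last day | yes |
| Washout 1, to day 56 | day 44 | none | no |
| Cycle 2, from day 56 | none | dose-increase days and last day | yes |
| Washout 2, to day 112 | 2 days in | none | no |

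The form completed on the last treatment day looks back one hour, so it cannot record what follows stopping.

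**4. By sequence.** In the placebo-first group (25 planned), the only study time after CBM is the second washout, so everything after CBM stops lies outside the comparison. In the CBM-first group (25 planned), the time after CBM is the first washout, outside the comparison, and then the placebo cycle, inside it.

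**5. How much could be missed (illustration only).** The documents give neither onset nor duration. Assume that a symptom is found only if present on day 2, that it lasts L days with L at least 2, and that onset is uniform over the first w days, with w at least 2. The share found is then 2/w.

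| w (days) | Share found on day 2 |
|---|---|
| 2 | 100% |
| 3 | 67% |
| 5 | 40% |
| 7 | 29% |
| 14 | 14% |

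If onset is uniform over 14 days and the end-of-washout questionnaires also detect the symptom, the share is (2 + L)/14 for L up to 12. This gives 4/14 = 29% for a 2-day symptom and 9/14 = 64% for a 7-day symptom. The result depends on the assumption, so no single figure can be given.

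**The case against.** **Washout is not unobserved.** The sentence on twice-weekly nurse meetings is not limited to the treatment cycles; if they continue, they add about 2 × 2 = 4 contacts per washout. The Discussion sentence on the treatment cycles concerns physiological measures and does not mention the adverse event discussion. Participants also live in facilities with 24-hour care and are followed by the same staff member throughout. This stands to the extent that it would be wrong to say that 12 of 14 days have no safety contact: whether the meetings continue is unclear. But they are described as discussing adverse event records, and no form is scheduled in washout.

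**The NPI-NH on days 56 and 112 overlaps with the form.** It covers anxiety, depression, sleep and appetite, among others. This stands for behavioural effects still present at those visits. They would enter as outcome scores and not as safety events. Day 56 is also the cycle 2 baseline, and baseline measures are covariates in the models. Night-time disturbance and appetite join the NPI-NH total only in special circumstances.

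**The recording tool is unstated.** The article does not say how the day-2 review is recorded. That no form is used there is an inference from the form's schedule, so the point is limited to what is scheduled.

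**Attribution of washout events is a matter for the analysis plan.** Often it is. Here the article itself fixes the periods compared, and washout is not among them. If the analysis plan already assigns these events, that part is settled by saying so.

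**Conclusion.** The point holds as a mismatch between stated schedules. Withdrawal is named as a risk and reviewed once per washout, on day 2. The form that feeds the adverse event record is not scheduled in washout, and the comparison as worded leaves washout out. The firm sizes are 12 of 14 days without a further dedicated review and, in the placebo-first group, all follow-up after CBM outside the comparison. This is a worthwhile, inexpensive improvement and not a fatal flaw.

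Three stronger readings are not supported:

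- **Most withdrawal would go undetected.** This needs onset and duration, which are not given. The illustration runs from 14% to 100% found on day 2. A share of calendar days is not a share of events.
- **The CBM–placebo difference is biased toward zero.** This would need a withdrawal symptom in the CBM-first group to outlast the 14-day washout and then be recorded in the placebo cycle. It is possible in one sequence only, and no figure in the article bears on its size.
- **Early stoppers get no withdrawal review.** The article says only: "In the instance where a participant withdraws halfway through a treatment cycle, the information collected prior to withdrawal will be retained". It neither describes nor excludes follow-up after early stopping, which a condensed article commonly leaves to the full protocol. The attrition allowance is no count of people who stop on CBM.

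**What to change.** 1. Complete the existing adverse event form at the day-2 washout review and at the day-56 and day-112 visits, with the question covering the time since the last record instead of the last hour. On day 56, complete it before the first cycle 2 dose.
2. In the adverse event comparison, assign events in a washout to the treatment that preceded it, and also report them separately so that on-treatment and post-treatment events can be told apart.
3. Reconcile the Abstract, the safety section and the Discussion on how often the research nurse sees participants and whether these meetings continue in washout.

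**Cost.** No new visits or staff: one short form at three existing contacts and a line or two in the analysis text. The downside is a few minutes per visit and a recall window of about 12 days (day 44 to day 56) in participants with memory impairment. Care staff should therefore contribute to the form, as they already do during titration.

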### Measures

**The Neuropsychiatric Inventory Questionnaire–Nursing Homes** (NPI-NH) [46] is a questionnaire that measures 12 neuropsychiatric symptoms (delusions, hallucinations, agitation, depression, anxiety, euphoria/elation, apathy/indifference, disinhibition, irritability, aberrant motor behaviour, night-time disturbances and appetite changes). The frequency and severity of each symptom is rated (4-point and 3-point Likert scales). A total score can be calculated by adding the first 10 domains together, and all 12 domain scores can be summed in special circumstances where neurovegetative symptoms are of interest, and a carer disruptiveness score (summing the disruptiveness score of the 10 [or 12] behavioural domains) can be calculated. The NPI-NH can be completed in approximately 10 min.

**The Cohen-Mansfield Agitation Inventory** (CMAI) is designed to assess agitation cross three domains, namely physically aggressive behaviour, physically non-aggressive behaviour and verbally agitated behaviour [47]. The CMAI comprises 29 items, uses a 7-point Likert scale (never = (1), less than once per week = (2), once or twice per week = (3), several times per week = (4), once or twice per day = (5), several times per day = (6), several times per hour = (7)), and measures four subscales: aggressive behaviour, physically non-aggressive behaviour, verbally agitated behaviour, and hiding and hoarding. A total score of 203 is calculated, with a higher score indicating a higher frequency in behavioural occurrence, and the measure takes approximately 5 min to complete.

**The Quality of Life in Alzheimer’s Disease** (QOL-AD) instrument is designed to measure aspects important for an individual’s QOL. The QOL-AD consists of 13 items using a 4-point Likert scale (poor = (1), fair = (2), good = (3), and excellent = (4)) and is designed for both self-report and proxy report [48]. The QOL-AD measures four domains (physical health, mental health, social, and function) and can be completed with people with a wide range of dementia severity [49]. A total score out of 52 is calculated, with a higher score indicating a higher QOL. The self-report version can be completed in about 10–15 min and the proxy report in about 5 min. A composite score can also be calculated (participant QOL-AD × 2 + carer QOL-AD × 3).

**The Abbey Pain Scale** comprises six items assessing vocalisation; facial expression; change in body language; and behavioural, physiological and physical changes [50]. This questionnaire uses a 4-point Likert scale (absent = 0, mild = (1), moderate = (2), severe = (3)), and a total score out of 18 is calculated. The severity of pain is indicated as mild (score of 3–7), moderate (8–13) and severe (14+) and can be completed in less than 5 min.

### Process evaluation outcomes

The one-page pre- and post-surveys will be administered to aged-care staff and next of kin at the beginning of the first treatment cycle and at the end of the second treatment cycle. These surveys comprise seven to nine questions regarding individuals’ perceptions towards CBM oil use and the symptoms of dementia they find most challenging. A total of six questions will be asked during the focus group discussions. These questions relate to positive and negative observations among those taking CBM oil, as well as changes in perceptions, knowledge and benefits regarding the use of CBM use.

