### Blinding

This is a double-blind study. Therefore, the laboratory manager will be the only individual who will know the group allocation for the participants. This is to ensure that the pharmacist, aged-care staff, medical practitioners, research nurse, family members/next of kin, participants and researchers are all blinded to the participant’s group allocation. Once the study is complete, the laboratory manger will un-blind the information by providing the primary researcher with a list of participants and their group allocation in order to conduct the analysis.

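### The focus groups ask blinded staff and family what they observed under CBM oil, and no stated step ties a remark to the CBM or the placebo cycle

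*Protocol article*

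**What the plan says.** All references are to the protocol article.

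- **Exposure.** Under Methods/design in the Abstract, each participant receives CBM oil or placebo in the first six-week cycle and the other product in the second.
- **Blinding.** The Blinding section states that "the laboratory manager will be the only individual who will know the group allocation for the participants" and lists those kept unaware: "aged-care staff, medical practitioners, research nurse, family members/next of kin, participants and researchers are all blinded to the participant’s group allocation".
- **Unblinding.** The same section has the laboratory manager release the order once the study is complete by "providing the primary researcher with a list of participants and their group allocation in order to conduct the analysis". It names no other recipient.
- **Timing of the groups.** Methods and general study design says: "At the end of the second treatment cycle, the residential aged-care staff and family members will be asked to participate in a follow-up focus group". The stated purpose there is in-depth information on "individuals’ perceptions before and after the administration of CBM".
- **Content.** Process evaluation outcomes mentions six questions and says of them: "These questions relate to positive and negative observations among those taking CBM oil". The sentence then adds changes in perceptions, knowledge and benefits relating to CBM use.
- **Analysis.** The Qualitative subsection of Data analysis describes repeated reading, open coding and line-by-line coding of transcripts into themes. Its safeguards are reflectivity by the interviewer, member checking and verbatim quotes.

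**The concern.** The question asks an informant to report what was seen during a specific exposure, and the trial is built so that the informant does not know when that exposure took place. An answer can rest on a guess about the order, on the resident's whole time in the trial, or on prior belief about cannabis. The transcript would not show which of these it was.

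What is at stake is the part of the qualitative work that speaks to observed benefits and harms. The Discussion says the qualitative phase matters because little is known of personal views on CBM use and of its effects in this setting. If remarks about placebo weeks are counted among observations on CBM, the resulting themes mix drug, placebo and expectation. A reader who meets them beside the randomised result could take them for independent support.

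**Working it through.** The plan gives no figure for this component, so the check consists of setting its statements side by side.

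1. **Can informants know the CBM cycle when asked?** The Blinding section leaves only the laboratory manager informed until the study is complete. The groups meet at the end of the second cycle, which Data collection places at day 97, while the last questionnaires are due at day 112. No section says that staff or relatives are told the order, before or after the groups. Study completion is used loosely: Methods and general study design puts the post-surveys at completion of the study, while Process evaluation outcomes puts them at the end of the second cycle. Even if the groups met later, unblinding is described for the primary researcher only.

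2. **How much of the exposure is placebo?** Two cycles of 6 weeks make 12 dosing weeks per resident, of which 6 are placebo: 6/12 = 50%.

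3. **Which product was taken most recently?** Randomisation allocates 25 residents to each order. For the 25 given CBM first, the CBM cycle ends at day 42. By day 97 that is 97 − 42 = 55 days, or about 8 weeks earlier. For half of the residents as randomised (25/50), the freshest six weeks of dosing are placebo weeks.

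4. **Does the group format help?** Participants and setting foresees six groups of six to eight people. Nothing separates informants by sequence, so one group may discuss residents from both orders.

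5. **Does the analysis restore the link?** Open and line-by-line coding produces themes. Member checking shows whether informants' views were captured faithfully, and verbatim quotes show what was said. Neither shows whether the informant had the right cycle in mind. The interviewer's reflectivity cannot help either, since the researchers are blinded until the study is complete. No step assigns a remark to a resident, a cycle or the released list, and a general remark cannot be assigned to one afterwards.

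6. **Illustration only.** Suppose each informant describes the one cycle believed to be CBM, and that both cycles prompt equally many remarks. If a proportion p picks correctly, the share of remarks that belong to placebo is 1 − p: 50% at p = 0.5, 30% at p = 0.7, and 0% at p = 1. Both suppositions and all values of p are assumptions; the documents give none of them.

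**The case against.** **The component is about perceptions.** It is labelled exploratory and qualitative, and most of its content concerns attitudes to CBM, knowledge, and the practicalities of its use in a care facility. Blinding does no harm to these topics. This stands, and it limits the point to the observation strand. It does not remove that strand, because Process evaluation outcomes lists observations in those taking CBM separately from changes in perceptions.

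**The interview guide is not shown.** The article summarises six questions in one sentence, and the guide may already ask by cycle. That is possible, and a missing guide or coding frame would be no finding in itself. But the question content, timing, blinding, recipient of the allocation list and analysis are all stated, and as stated they do not fit together.

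**The before/after purpose is correct.** A reader might infer that describing perceptions before and after CBM is also an error. It is not: by the end of the second cycle every resident still in the trial has received CBM in one of the cycles, so the comparison of attitudes holds in either order.

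**The harm is not documented.** A reader might infer that placebo-cycle observations will be reported as CBM effects, or that the whole process evaluation fails. The article says neither. Some informants may identify the cycle from visible effects, and nothing says how the themes will be presented. What the text supports is that such reporting can happen and that no stated step would prevent it.

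**Asking for guesses could affect ratings.** Inviting informants to guess the order in a group near day 97 comes before the day-112 questionnaires, and under Rigor one staff member may follow several residents. This objection is sound and shapes the fix.

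**Conclusion.** The point holds for the observation strand of the focus groups. Blinded informants are asked about a period they cannot identify, and no stated step links their remarks to a cycle or to the released allocation. As described, the strand cannot separate CBM from placebo, and placebo-cycle observations can be reported as CBM effects.

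The only size the documents support is the exposure: 6 of 12 dosing weeks per resident are placebo, and 25 of 50 residents take placebo in the more recent cycle. The actual extent of misattribution is unknown, and the percentages from assumed guess rates are not estimates.

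The conclusion assumes that the groups run as described and that informants are not told the order beforehand. The attitude strand, the NPI-NH analysis and the sample size are untouched. This is a worthwhile correction to an exploratory component, not a threat to the trial's main result.

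**What to change.** 1. Word the observation questions by first and second treatment cycle for the resident concerned, without naming a product. Leave the questions on attitudes to CBM as they are.
2. Code each remark by resident and cycle, and attach the product only after the allocation list is released.
3. Report remarks that cannot be tied to a cycle as general perceptions formed under blinding, not as observed effects of CBM.
4. If informants' guesses of the CBM cycle are wanted, collect them individually and only after that informant's last outcome rating, which is day 112 of the last resident they rate. Do not collect them in the group.

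The cost is a rewording of the observation questions, one more coding field and slightly longer discussions, most noticeably where group members know different residents. The change must be in place before the groups meet. It does not alter the blinding, the outcome schedule or the quantitative analysis.
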